#### Primary outcome measures

##### Revised dyadic adjustment scale

The DAS-R (Busby et al., 1995; Portuguese validation by Pereira et al., 2017) is a self-rating questionnaire with 14 items designed to assess the dyadic marital adjustment through three dimensions: Consensus (items 1–6 rated on a Likert-type scale range between 5 - always agree to 0 – always disagree), Satisfaction (items 7–10 rated on a Likert-type scale range between 0 - all the time to 5 – never) and Cohesion (items 11–14 rated on a Likert-type scale range between 0 − never to 5 – more often). Higher scores indicate greater marital adjustment. The internal consistency of the overall scale in original version was 0.90 (Busby et al., 1995) and in a Portuguese validation it was 0.89 (Pereira et al., 2017).

##### Marital social-skills inventory

The MSSI (Villa and Del Prette, 2012; Portuguese version Aguiar et al., 2018) is a self-report measure that evaluates the frequency with which people present social behaviors that are of critical importance to a satisfactory marital relationship. Questionnaire has 17 items and four dimensions: Expressivity (item 10, 16 and 17; *α* = 0.83), Self-affirmation (item 1, 6, 7, 8, 9, 11, 12 and 14; *α* = 0.66), Self-control (item 4, 5, 13 and 15; *α* = 0.69) and Assertive Conversation (item 2 and 3; *α* = 0.55). Each dimension is rated on a Likert-type scale, ranging from definitely believe this is not true (1) to definitely believe this is true (5). Higher scores indicate greater marital social skills.

#### Secondary outcome measures

##### Stepparenting attitudes and beliefs

SAB can be obtained through a questionnaire developed for this protocol (see Appendix A) based on previous stepparenting cognition research (see Fine and Kurdek, 1994). Seventeen items are used to rate the participants’ *attitudes and beliefs* addressed in the program content, such as *“initially, discipline and authority in the child’s education should be imposed by the biological parent.”* on a 5-point scale ranging from 1 = *strongly disagree* to 5 = *strongly agree*. Higher scores indicate greater stepparenting positive attitudes and beliefs.

##### Co-parenting attitudes and beliefs

A specific questionnaire was developed for this protocol with nine items related to CAB based on the co-parenting belief inventory (Pringle and Ehrenberg, 2005; Pringle, 2008; see Appendix B). Items like *“Parents should not involve their children with details of the divorce process”* are rated on a 5-point scale ranging from 1 (*strongly disagree*) to 5 (*strongly agree*). Higher scores indicated greater co-parenting positive attitudes and beliefs.

##### Remarriage belief inventory

The RMBI (Higginbotham and Adler-Baeder, 2008a) can be used to assess participants’ beliefs regarding remarriage and stepfamilies in general. There are 19 items in the Portuguese version (Santos et al., 2022), distributed among seven subscales: (1) adjustment (4 items), (2) stepfamilies (2 items), (3) priority (3 items), (4) past (2 items), (5) partner (4 items), (6) success (4 items) and (7) finances (3 items). Each dimension is rated on a Likert-type scale, ranging from definitely believe this is not true (1) to definitely believe this is true (5). The Cronbach’s alpha for the total scale was in original version was 0.73 (for females) and 0.72 (for males; Higginbotham and Agee, 2013) and in Portuguese validation was 0.72 for the total scale (Santos et al., 2022). Higher scores indicated stronger remarital beliefs.

##### Systemic clinical outcome routine evaluation (SCORE-15)

The SCORE-15 (Stratton et al., 2010; Pereira, 2011; Vilaça et al., 2017) is a self-report questionnaire to provide an evaluation of family functioning with 15 items and three dimensions: Family strengths (FS), Family communication (FC) and Family difficulties (FD). Each dimension is rated on a Likert-type scale, ranging from “describe us: very well” (1) to “describe us: very bad” (5). The internal consistency of the overall scale in original version was 0.89 (Stratton et al., 2010) and in European Portuguese validation was 0.88 (Vilaça et al., 2017). Higher scores correspond to greater difficulties in family functioning.

#### Feasibility measures

An intervention fidelity plan will be conducted by accessing participants’ *GSteps* receptivity (e.g., satisfaction, usability, knowledge learned). Questions were based on previously feasibility measures used in context of web-based intervention that promoted positive parenting (Suárez et al., 2018). First, the *Program Satisfaction Scale (PSS)* will be used (Suárez et al., 2018) to provide an evaluation of satisfaction with intervention. This measure is a self-report questionnaire with 14 items and three dimensions: Usability (items 1, 2, 3, 4), Content (items 5, 6, 7, 8, 9), and Parenting impact (items 10, 11, 12, 13, 14). Usability dimension is rated on a Likert-type scale, ranging from “very difficult” (1) to “very easy” (5). Content and Parenting impact dimensions are rated on a Likert-type scale, ranging from “strongly disagree” (1) to “strongly agree” (5). Item 8 and 9 are edited for semantic adjustment due to the “Game” nature of the program.

Second, the *Intervention Perceived Benefit (IPB)* will be used to assess the participants knowledge learned after the intervention. Adapted from Adler-Baeder (2007), twelve questions were elaborated for this study (see Appendix C in online supplementary material) according to *GSteps* content. Responses must be given on a 5-point Likert scale, ranging from “strongly disagree” (1) to “strongly agree” (5). Higher scores correspond to greater knowledge learned.

Third, a purposive sampling method will also be used. This method is an intentional selection of participants based on their characteristics (Etikan et al., 2016) who are knowledgeable about a specific issue (Creswell and Plano Clark, 2011). Six participants from *EG* that completed the entire *GSteps* program (including follow-up assessment) will be selected to answer one open question related to participant’s experience - *Please describe your opinion whether the GSteps content realistically represents familiar situations that you have experienced*. These six participants will be (a) two individuals from complex stepfamilies (a man who is simultaneously father and stepfather and a woman who is simultaneously mother and stepmother) and (b) four individuals from simple stepfamilies. Two of them from a stepfather-family (a stepfather and a mother), and the other two from a stepmother-family (a father and a stepmother). In this way, we considered individuals from all possible configurations of stepfamilies, aiming to acquire more realistic feedback regarding their experience as *GSteps* “players.” Based on qualitative approach, IRAMUTEQ software (Lahlou, 2012; Camargo and Justo, 2013) will be used to conduct textual analysis.

## Procedure

### Recruitment and randomization

*GSteps* can be called an intervention, psychoeducational activity, or “Game.” Recruitment will be announced in social media (i.e., Facebook, Instagram, Self-help forums) or through a project website. On all these platforms, a link to an online questionnaire (*T_0_* – pre-test assessment) should be available. Participants meeting inclusion criteria and consenting to enter the study proceed and complete the pre-test questionnaire. After that, an automatic equation set will randomly (1:1) allocate participants to the EG or to the CG. Based on the random assignment, an automatic message is sent. Participants in the EG are invited to play *GSteps* and receive an email with a link and a confidential username and password. Participants allocated in CG receive an email informing them that they are on the waiting list. Both participants and the research team will be blind to the assignment.

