## Methods and analysis

### Study design

This study protocol is a two-arm double-blind prospective RCT comparing a web-based psychoeducational intervention to a waiting control condition among adults in stepfamilies (*N* = 112). The proposed intervention consists of a three-module (Figure 1) interactive Game that lasts a minimum of 30 and a maximum 60 min and can be played over the course of 1 month in computer. Modules are sequential and focus on the romantic relationship, co-parenting and step-parenting. Assessments are made before (*T_0_*) and 1 month after the intervention (*T_1_*). The experimental group (EG) has a second follow-up after 2 months (*T_2_*). The control group (CG) is on a waiting list until completion of *T_1_*, and then gets access to the intervention. Intervention and measurements are carried out online. The protocol uses the learning app H5P and *Limesurvey* survey design tool integrated into Moodle e-learning management system. The use of H5P interactive teaching aids to solve problems has been studied in literature as an important tool for educational context (Wang et al., 2016; Sinnayah et al., 2021). Figure 2 displays the study schedule of enrollment, interventions and assessments. This RCT will follow the SPIRIT guidelines (Chan et al., 2013a, 2013b) and the CONSORT statement (Moher et al., 2010; Schulz et al., 2010).

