Each module lasts between 10 and 20 min. Each is presented in a sequential video dramatization with some or all family members portraying relationship challenges (components). Videos freeze to ask participants which would be the better option in the face of a given conflict. Participants are able to see how their chosen option could play out. There are *right*, *wrong*, and *not the best* options, and a message pops up with a psychoeducational content focusing on positive and successful practices of stepparenting, co-parenting and remarital functioning to guide the participant to the right answer. All videos have subtitles to facilitate participants’ comprehension. For example, in module 2, the participant will see an argument between Maria and her stepfather on what Maria said – *You are not my father! Do not order me!* Then, the video freezes and a question pops up – *What would be Antonio’s best answer?* The participant will have three options – (1) *Punish Maria*; (2) *Ask Maria’s mother for help*; (3) *Explain to Maria what is his role within the stepfamily* and (4) *Watch the video again*. If the participant chooses option one (wrong option), he/she will see a video with António punishing Maria and Maria denying him authority. Then, the video freezes and a psychoeducational massage will appear – *initially, discipline and authority must be imposed by the biological parent; Maria and António have not yet developed a trust relationship, because of that, she has difficulties in recognizing his authority*. Option two is the “not the best option.” If selected, another psychoeducational massage arises – *While it is very important for the biological parents to support the decision of the stepparents, it is even more important for the stepparents to clearly assume their role within the family. How could António assertively tell Maria what is his role in the family?* Only option three is correct and if participant choose it, he/she will see the correct video with the correct behavior and the Game goes forward (see the sequence of images in Figure 4). Participants are encouraged to finish all modules and have the opportunity to communicate with a mental health professional for clarification of doubts or emotional support, if desired. The Game platform is checked daily to monitor participation. Participation reminders are sent weekly to finish the *GSteps* in the allotted time – 1 month.

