**Figure 4 fig4:**
[figure not shown]
Branching scenario from Scene 10 of Module 2-“Stepparenting.”

*Wait-list*. After replying to the baseline questionnaire (*T_0_*), participants assigned to this condition receive a message informing that they are on the waiting list to participate on the course. The wait-list CG is also notified that they will be receiving further instructions in 1 month, and that access to the course is be possible after replying to a second assessment (*T_1_*).

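### The trial is labelled double-blind, but participants are told their arm, and the article does not show how the research team stays blind

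*Protocol article*

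**What the plan says.** The Study design section of the protocol article describes a "two-arm double-blind prospective RCT" against a waiting control condition. The Recruitment and randomization section ends with the statement "Both participants and the research team will be blind to the assignment".

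The same section sets out what happens after allocation. An automatic procedure assigns participants 1:1, and then: "Based on the random assignment, an automatic message is sent". Those in the experimental group (EG) are invited to play and "receive an email with a link and a confidential username and password". Those in the control group (CG) "receive an email informing them that they are on the waiting list". The wait-list paragraph under GSteps development repeats this: "participants assigned to this condition receive a message informing that they are on the waiting list". It adds that access follows only after the T1 assessment.

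On conduct during the intervention month, GSteps development says: "The Game platform is checked daily to monitor participation". Weekly reminders to finish also go out, and players may contact a mental health professional. The Feasibility measures section has six EG completers chosen by family role to answer an open question.

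Strengths and limitations acknowledges that all instruments are self-report.

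**The concern.** Double-blind is a specific claim about protection against bias. It tells a reader that neither the participant nor the team could let knowledge of the arm influence the data. Here the participant is also the outcome assessor on every efficacy scale. If participants know their arm, the label claims a protection on the very outcomes that lack it.

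What is at stake is how the T1 contrast between EG and CG is read. Someone who has been given the program may answer more favourably because improvement is expected, and someone told to wait may answer differently for that reason alone. Neither randomization nor the planned analysis removes such an effect. An uncorrected label would also carry into the results report, which the article says will follow CONSORT.

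**Working it through.** No arithmetic beyond a count applies: the point challenges no sample size, power or effect figure. The check sets the statements side by side.

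**1. Participants.**
- Claimed: participants are blind (Recruitment and randomization), and the trial is double-blind (Study design).
- Described: the message depends on the arm. EG gets an invitation and login; CG is told it is waiting, and is told so again in the wait-list paragraph.
- Comparator: no Game access until T1 is completed (Study design). No sham program or attention control is described.
- Result: a person who holds a login and plays knows that the intervention is being given; a person told to wait knows that it is not. The claim and the procedure cannot both stand, and no detail in a fuller protocol could reconcile them while these messages are sent.

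**2. Research team.**
- Before T1, only EG participants have Game access (Study design; wait-list paragraph). Anyone who monitors play or supports players in that period can tell who is in EG.
- The daily check and the reminders are described without naming who carries them out. Allocation and the first message are automatic, so the reminders may be automatic too. The article does not say that the mental health professional belongs to the research team.
- The six interviewees must be EG completers, so whoever selects them must know the arm. That selection requires completion of the follow-up assessment, so for those six it comes after their outcome data.
- Result: the blanket claim for the team is unexplained, and doubtful as it stands. It is not directly contradicted in the way the participant claim is.

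**3. Outcomes exposed.**
- Primary: DAS-R and MSSI, 2 scales.
- Secondary: stepparenting attitudes (SAB), co-parenting attitudes (CAB), RMBI and SCORE-15, 4 scales.
- 2 + 4 = 6 scales. By the article's own statement that all its instruments are self-report, 6 of 6 are rated by the participant.
- The exposure is concrete for SAB. Its sample item, on the biological parent taking the lead in discipline at first, closely matches a message shown to players in Module 2. Agreement at T1 could reflect a changed belief or simply giving the answer the program favours.

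**4. Limitations.** Strengths and limitations lists response-set tendency from self-report, dropout during the intervention, and missing follow-up data. Knowledge of allocation is not among them.

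**5. Could the analyst be masked by coding the arm?** Not in the dataset as described. T2 is collected for EG only (Study design; Instruments and measures). Instruments and measures restricts the intervention-quality and perceived-benefit outcomes to the experimental condition. The planned mixed ANOVA uses three time points for EG and two for CG (Data and statistical proposed analysis). Whichever code carries T2 data is EG, so relabelling the arm variable conceals nothing.

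**The case against.** The strongest defence is that the authors meant allocation concealment. Automatic assignment after the baseline questionnaire may well conceal the allocation up to that point. But concealment ends at assignment, whereas the sentence speaks of being blind to the assignment and the Study design section applies the label to the whole trial. If concealment was meant, the wording still needs correcting.

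A second defence is that the reader is not badly misled: the abstract names a wait-list control, the arm-specific emails come immediately before the blinding sentence, self-report is disclosed, and the discussion and conclusion make no blinding claim. This stands in part. It limits the harm but does not make the label true.

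Three stronger readings are tempting, and the article does not support them:
- A reader might infer that the research team itself tracks EG play every day and is therefore unblinded. The text names no actor, a separate operator is possible, and a journal article may leave such detail to a fuller document. What can be said is that the article does not explain how the team stays blind.
- A reader might infer that the bias must favour EG. That is plausible, but nothing in the article shows it. CG members are told to expect instructions in one month and access after T1, which could produce anticipation as easily as disappointment.
- A reader might infer that the limitations are silent apart from response-set tendency. They also list dropout and missing follow-up data. The gap is the narrower one of knowledge of allocation.

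**Conclusion.** The point holds and should be corrected before results are reported. For participants, the double-blind label and the blinding sentence are contradicted by the article's own procedures, and this alone defeats the label. For the team, blinding is doubtful and unexplained; the article does not establish that it is broken.

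The exposure covers all participants and all six primary and secondary scales. The size of any resulting bias cannot be derived from the article. That it would favour EG is an assumption and should be written as one.

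This is an internal contradiction about a stated design property, not an objection to using a wait-list. Randomization, outcomes, sample size and the analysis model are unaffected.

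**What to change.** - Delete the double-blind label in Study design and the claim in Recruitment and randomization that participants are blind.
- State instead that participants know their allocation, and that allocation is generated automatically after the baseline questionnaire.
- State which roles, if any, are masked and how. Include who monitors the platform, who sends reminders and who selects the six interviewees.
- If the analyst is to be masked, run the primary T0/T1 comparison on a coded file from which T2 and all EG-only measures have been removed. Release the full data once that comparison is final.
- Add self-report by participants who know their arm to Strengths and limitations, and qualify the efficacy conclusion to match.

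The cost is mostly wording, and the stated design will look less strong. Masking the analyst, if chosen, also requires someone outside the analysis to prepare the restricted file, which is more work than recoding the arm variable.

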### Eligibility criteria

All interested adults are required to complete screening questionnaires prior to randomization process. Inclusion criteria are (1) being in a stepfamily as a result of remarriage or repartnering; (2) length of current marriage/cohabitation of at least 6 months prior to enrollment; (3) having children from past relationships and/or stepchildren; (4) having access to a computer with internet connection; (5) to be native of the European Portuguese language. Subjects in a remarriage after widowhood (at least one of the partners is not divorced) are excluded. Furthermore, participants have to agree to participate *via* electronic informed consent and be willing to provide an e-mail address for contact during the study.

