**Methods/design:**

A RCT design is presented to evaluate the outcomes of a self-administered, interactive and web-based psychoeducational Game targeting dyadic marital adjustment and interpersonal skills as the primary outcomes and remarriage beliefs, family function and stepparenting and co-parenting attitudes as the secondary outcomes. Other outcome measures include satisfaction with *GSteps*, participants’ knowledge learned after the intervention and a purposive sampling method will be used to access feasibility. The minimum required sample size is 112 participants (56 per condition) randomly allocated either to an experimental group (EG), receiving *GSteps* intervention, or to a wait-list control group (CG). A survey is conducted electronically. Assessments take place at baseline (*T_0_*), after the intervention (*T_1_*) and 1-month follow-up (*T_2_*).

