### Aims

To fill the gaps in the literature, our protocol intends to evaluate the efficacy and feasibility of a new web-based psychoeducational intervention (*GSteps*). The protocol outlines a comparison with a non-intervention control condition in a sample of Portuguese speaking adults in stepfamilies (parents and stepparents). The protocol offers options to examine changes in *stepparenting and co-parenting attitudes, remarriage beliefs, dyadic marital adjustment, marital social skills* and *family function.*

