## Strengths and limitations

Several strengths of the protocol and its design must be highlighted. This is a program that focuses on adults in stepfamilies, a vulnerable and understudied group, namely in the Portuguese context. This protocol underlines the importance of adapting psychoeducational intervention programs to the current demands of everyday life, namely, the exponential use of technological and virtual resources. Furthermore, literature suggest that online interactive multimedia programs can offer effective delivery of general education content (Cairncross and Mannion, 2001; Gelatt et al., 2010). As with other web-based interventions, this approach has a brief format, is low-cost and has a broad reach. The existence of subtitles in all videos enhances this reach and makes it possible to adapt the *GSteps* to other languages. Furthermore, it is a very comfortable type of intervention in which participants can receive the intervention from computer-devices in their own homes.

Moreover, by performing repeated measurements of psychosocial variables related with marital domain (dyadic marital adjustment; marital social skills; remarriage beliefs), parenting domain (SAB and CAB) and family functioning through a longitudinal and RCT design, this research protocol facilitates more reliable data on the outcome effects of the intervention. There are also some limitations of the protocol. All included measurement instruments are self-reports that can lead to a response-set tendency. Nonetheless, the majority of instruments are standardized inventories with good levels of reliability and validity or instruments that are tailor-made for the protocol. An expected limitation is the dropout rate during the intervention process as well as a significant missing data to follow-up assessment. To minimize this limitation, participants should be regularly notified by email to continue/end the *GSteps* or to participate in the post-and follow-up assessments.

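### The stated rules let both partners of a couple enrol; such couples would be split across arms about half the time, probably pulling the couple outcomes toward no difference

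*Protocol article*

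**What the plan says.** Recruitment is open: "Recruitment will be announced in social media (i.e., Facebook, Instagram, Self-help forums) or through a project website" (Recruitment and randomization). After the baseline questionnaire, "an automatic equation set will randomly (1:1) allocate participants to the EG or to the CG", so the unit of allocation is the individual.

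The Eligibility criteria section states that "All interested adults are required to complete screening questionnaires prior to randomization process". It lists five inclusion criteria and one exclusion, for remarriage after widowhood. The third inclusion criterion is "having children from past relationships and/or stepchildren", which the parent and the stepparent of one household can each meet. The Aims section names both roles as the target sample. Nothing in the article limits enrolment to one partner, links partners, or allocates them together.

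The abstract describes the Game as "targeting dyadic marital adjustment and interpersonal skills as the primary outcomes". The first of these is measured by the DAS-R, "designed to assess the dyadic marital adjustment through three dimensions" (consensus, satisfaction and cohesion). The second is measured by the MSSI, which rates social behaviours within the marriage. The Strengths and limitations section notes that "participants can receive the intervention from computer-devices in their own homes". The control group (CG) waits until T1 for access.

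**The concern.** Two partners who both enrol report on the same relationship. If one is in the experimental group (EG) and the other is on the waiting list, the waiting partner lives with someone who is learning communication and conflict management, which are listed components of Module 1. If the Game works as intended, the waiting partner's scores could move too, even if that partner never opens it. The contrast between arms would then shrink on the two outcomes that define success. No analysis can recover that loss afterwards. As described, no item even records which participants are partners, so the extent could not be checked.

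**Working it through.** **Inputs from the protocol article.** Individual 1:1 allocation (Recruitment and randomization). From Power analysis: d = 0.5, alpha 0.05, power 0.80, 74 participants before dropout, about 50% dropout, 112 planned (56 per arm).

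**Inputs assumed.** p = share of participants whose partner also enrols (20%, 40%, 60%). s = share of the effect passed to the waiting partner (0.5 or 1). T0–T1 correlation r = 0.65. Analysable sample 28 v 28, from 112 × 0.5 = 56. Tests two-sided.

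**The plan's own figure.** A two-group ANCOVA at d = 0.5 (f = 0.25) needs 128 if the covariate explains nothing. It needs about 75, close to the stated 74, when r is about 0.65. That is the reason for using r = 0.65 here; the article does not state it.

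**Step 1, chance of a split.** Independent allocation: 0.5 × 0.5 + 0.5 × 0.5 = 0.50. With arms fixed at 56 and 56: 56/111 = 0.505.

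**Step 2, share of the CG with a treated partner.** p/2 = 10%, 20%, 30%.

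**Step 3, diluted effect.** d_eff = 0.5 × (1 − s × p/2). For example, p = 0.4 and s = 0.5 gives 0.5 × (1 − 0.10) = 0.45.

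**Step 4, power with 28 per arm (noncentral t).** ANCOVA: the effect is d/√(1 − r²) = d/0.760 and the noncentrality is that times √(28/2) = 3.742. At d = 0.50 this is 0.658 × 3.742 = 2.46, power 0.68. The planned group-by-time interaction on T0 and T1 is a test on change scores, with effect d/√(2(1 − r)) = d/0.837. At d = 0.50 the noncentrality is 2.24, power 0.59.

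| p | s | d_eff | ANCOVA power | Group × time power |
|---|---|---|---|---|
| 0 | – | 0.50 | 0.68 | 0.59 |
| 0.2 | 0.5 | 0.475 | 0.63 | 0.55 |
| 0.4 | 0.5 | 0.45 | 0.59 | 0.51 |
| 0.6 | 0.5 | 0.425 | 0.54 | 0.46 |
| 0.2 | 1 | 0.45 | 0.59 | 0.51 |
| 0.4 | 1 | 0.40 | 0.49 | 0.42 |
| 0.6 | 1 | 0.35 | 0.39 | 0.34 |

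If instead the 74 participants of the power analysis were all analysable (37 per arm), ANCOVA power would fall from 0.80 to 0.76, 0.71 and 0.66 (half spill-over) or to 0.71, 0.61 and 0.50 (full).

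**Step 5, does ignoring couples distort the test itself?** A t-test was simulated under no effect, with 56 participants, a within-couple ICC of 0.5 (assumed) and 40%, 60% or 100% of participants in couples. With individual allocation, type I error stayed at about 0.05 in each case. Same-arm and split couples contribute covariances of opposite sign to the arm difference, and these cancel on average. With both partners placed in one arm, the unadjusted type I error rose to between 0.07 and 0.11.

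**The case against.** The strongest objection is that the size is unknown. No section describes couples enrolling together; recruitment, consent and e-mail contact are individual. With p = 0 there is no effect at all. Full spill-over is an extreme case, since a partner who never plays would gain as much as the player. EG members who drop out, or play little, would pass on less. All of this stands, and it is why the figures are a range rather than an estimate.

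Access to the Game is by a confidential login, which makes casual sharing less likely. That is a partial barrier only: it does not stop an effect that travels through the relationship.

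A condensed article might omit a one-per-household screening item. But it does print the eligibility list and the allocation rule, and followed as written they admit split couples.

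A reader might infer two stronger things. The first is that contamination will occur. The documents do not support that; they only leave it open. The second is that the t-tests and ANOVAs are invalid because they treat partners as independent. Step 5 shows that this fails under the individual allocation the article describes.

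**Conclusion.** The point holds in conditional form. Individual allocation combined with the stated criteria permits couples to be split, and any couple in which both partners enrol has about a 50% chance of it. The likely consequence is bias toward zero on both primary outcomes. The size depends on four quantities that the documents do not fix: the share of couples, the spill-over, the T0–T1 correlation and the number analysable. It runs from nil to a loss of up to 0.15 in d (0.50 to 0.35) over the range examined. The matching ANCOVA power loss is from 0.68 to 0.39, with the planned interaction test lower throughout. The direction is probable rather than certain: the calculation assumes that the waiting partner can only gain, and that two treated partners do not reinforce each other. The matter should be settled before randomisation starts.

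**What to change.** Add one screening item asking whether the respondent's partner is already taking part, admit only one adult per couple, and state this in the eligibility criteria. The cost is one question and a few excluded second partners. It depends on honest answers, so some undeclared couples may remain.

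A second-best option is to place the second partner in the first partner's arm. This also removes the dilution, but it turns couples into clusters. A couple random effect then becomes compulsory, and there is a design effect of about 1 + p × ICC. With ICC 0.5 (assumed) and p = 0.2, 0.4 or 0.6 this is 1.1, 1.2 or 1.3. On the ANCOVA basis with 28 per arm, dividing the standardised effect by the square root of the design effect gives power of about 0.63, 0.60 and 0.56. That is hardly better than leaving half spill-over alone (0.63, 0.59, 0.54), although the estimate would no longer be diluted.
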